#### Quality of life

Self-rated mental health will be measured using the SF-36 questionnaire, mental component score, at baseline and after 3 and 6 months. The scale was translated into Chinese using a two-part method that included (a) translation by bilingual investigators and (b) back translation. The two versions (English and Chinese) of the instrument were compared and verified by a qualified, bilingual expert specializing in the design and cross-cultural validation of study questionnaires. The specific numerical values for each parameter will be compared.

#### Skin sympathetic nerve activity (SKNA)

This refers to the electrical activity originating from the nerve structure that can be measured on the surface of the skin to reflect sympathetic tone [21] and is recorded using three standard ECG patch electrodes and a prototype device with a wide bandwidth (16kHz) and high sample rate (10kHz). The three electrodes include two recording electrodes and one reference lead to form a bipolar recording channel. One pair of electrodes are placed in the right and left subclavicular areas as the negative and positive leads, respectively, and the third lead is placed below the right arcus costalis as the reference. The recorded electrical signals are analyzed by using custom written software, amplified and band-pass filtered (500–1000 Hz) to display SKNA. We also create an algorithm to quantify SKNA by calculating the eSKNA, which can indicate periods of nerve activation in the given time period. SKNA will be continuously recorded for 30 min at baseline and 3 and 6 months follow-up.

#### Inflammatory markers

Blood samples (10 ml) will be collected at baseline and at 3 and 6 months for measurement of inflammatory cytokines. The blood was then centrifuged to separate the serum and stored at − 80℃ in a refrigerator. Serum levels of inflammatory cytokines, including interleukin-1β, interleukin-6, and TNF-α, were measured using commercially available multiplex assays. All immunoassays will run in duplicate and read according to the manufacturer’s instructions. The investigators performing the cytokine assays will be blinded to group allocation.

### Adverse events

Any adverse events and their management will be recorded from baseline to 6 months. These adverse events may include, but are not limited to, hypotension, bradycardia, fainting, severe pain, and local infection.

### Data collection and management

#### Plans for assessment and collection of outcomes

All investigators will be trained in terms of the study protocol, the SF-36 questionnaire, and SKNA assessment execution. The data collection form (both paper-based and electronic case report form) will be provided for the entire research team. The first-time data collection by investigators will be conducted under the supervision of the principal investigators. Serum will be stored in a − 80℃ freezer with documented in a freezer log until used.

#### Plans to promote participant retention and complete follow-up

The investigators will make every effort to improve participants’ adherence to follow-up and treatment by providing routine health care online or by telephone. All study patients, except those who withdraw consent, will be included in the analysis during the course of treatment.

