#### Criteria for discontinuing or modifying allocated interventions

As a non-invasive treatment, LLTS carries a very low risk of potential harm. Adverse events may include, but are not limited to, hypotension, bradycardia, fainting, severe pain, and local infection. All adverse events and their management will be recorded from baseline to 6 months. Circumstances in which individual participants may discontinue or modify the intervention include the occurrence of intolerable or unexpected side effects during the course of the therapy, and other circumstances that would endanger participant’s health if they continued in the study, as well as at participant request.

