### Statistical plan

Descriptive statistics will be presented for baseline characteristics. Continuous variables are presented as mean ± SD or median (interquartile range), as appropriate. Categorical variables will be presented as proportions. Baseline variables will be compared between groups using Student’s *t*-test or Mann–Whitney *U* test for continuous variables and chi-square test for categorical variables. We will use a generalized estimating equation modelling approach to compare the outcome measure at the 3- and 6-month visits between the two groups after adjusting for the baseline measure [18]. Estimates reflect the exponentiated regression model terms and are interpreted as the ratio of the median responses in the active arm relative to the median response in the sham arm. Patients who discontinue the stimulation protocol and receive PVC ablation during the study period will be censored. These patients will be regarded as withdrawals from the study and the data from the last clinical follow-up will be included into final analysis.

Linear regression will be used to compare the association between the change in PVC burden at follow-up and measures of HRV and SKNA. Statistical significance will be set at *P* < 0.05 (two-sided). All statistical analyses will be performed using SAS software version 9.3 (SAS Institute, Cary, North Carolina).

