### Methods in analysis to handle protocol non-adherence and any statistical methods to handle missing data

The analyses will be done in intention-to-treat population including all patients who received intervention or sham intervention without major protocol deviations. Significant protocol deviations or complications (hypotension, bradycardia, fainting, severe pain, and local infection) and subsequent failure to obtain primary and secondary outcome data will be documented prior the database closure. In case of withdrawals and missing data, the last observation carried forward procedure will be applied where appropriate.

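### The protocol does not consistently separate stopping stimulation from leaving follow-up, so 6-month outcomes may be lost or replaced avoidably

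*Protocol article*

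**What the plan says.** Four sections of the protocol article bear on patients who do not complete stimulation.

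- *Criteria for discontinuing or modifying allocated interventions* lists grounds for stopping or changing the intervention. One is "the occurrence of intolerable or unexpected side effects during the course of the therapy". The list ends with danger to health "if they continued in the study, as well as at participant request". The section governs the intervention, but this ground is worded in terms of staying in the study.
- *Plans to promote participant retention and complete follow-up* states: "All study patients, except those who withdraw consent, will be included in the analysis during the course of treatment". It also promises effort on adherence to follow-up as well as to treatment.
- *Statistical plan* states: "Patients who discontinue the stimulation protocol and receive PVC ablation during the study period will be censored". It continues: "These patients will be regarded as withdrawals from the study and the data from the last clinical follow-up will be included into final analysis".
- *Methods in analysis to handle protocol non-adherence and any statistical methods to handle missing data* defines an intention-to-treat population "including all patients who received intervention or sham intervention without major protocol deviations". It foresees that primary and secondary outcomes may not be obtained after deviations or complications. It asks for this to be documented, and applies LOCF to withdrawals and missing data where appropriate.

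Two further sections set the measurement schedule. *PVC burden* plans the 10-day patch at baseline, 3 and 6 months, with no condition that stimulation continues. *Follow-up schedule* places visits at 3 and 6 months and describes the 6 months as the treatment duration.

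**The concern.** Stopping a self-applied ear stimulator and refusing further measurement are different events. The primary outcome is a patch recording, which can be made whether or not the patient still uses the device. Where the rules blur the two events, a site may reasonably stop measuring a patient who has only stopped stimulating, or an analyst may set aside values that were recorded.

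Why patients stop matters. Poor tolerability and lack of benefit are plausible reasons, and both may differ between tragus and earlobe stimulation. Outcomes dropped or replaced after randomisation for such reasons can make the arms less comparable. Carrying a month-3 on-stimulation value forward to month 6 for someone who has since stopped also credits the device with an effect it may no longer be delivering. An analysis plan written later can choose a better method, but it cannot supply a patch recording that was never made.

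**Working it through.** **Reading the rules side by side**

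| Patient | What the sections say |
|---|---|
| Stops at week 8 for ear pain, no ablation, still consents | *PVC burden*: patch due at 3 and 6 months. Retention section: included, but later data count only if the closing phrase means the 6-month period. Missing-data section: excluded if stopping is classed as a major deviation; if no later patch is obtained, LOCF carries baseline. |
| Stops after month 3 and has an ablation | *Statistical plan*: censored, regarded as a withdrawal, last follow-up data used. Retention section: included, since consent was not withdrawn. |
| Withdraws consent after month 3 | Retention section: left out, with no provision for the month-3 recording. Missing-data section: withdrawals are carried forward, so the month-3 value would be used if the term covers consent withdrawals. |
| Has a complication and no 6-month recording is obtained | Missing-data section: document the failure and apply LOCF. No step to obtain the recording is attached. |

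The first and third patients are treated differently depending on which section is followed. In the second and fourth, a clinical event leads to use of an earlier value although the patient has not refused measurement.

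**The plan's own figure**

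Inputs from *Sample size calculation*: 90 evaluable patients, 10% drop-out, 100 recruited, 50 per arm. 90 / (1 − 0.10) = 100, which reproduces the total. The plan therefore allows for 10 lost patients. The 90 cannot be reproduced, because no SD is given.

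**What measuring the stoppers would do to power**

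1. Effect: 40% of a 15% baseline burden = 6 percentage points, taken as the between-arm difference (assumption).
2. Implied SD: two-sample t-test, 45 per arm, two-sided 0.05, noncentrality (6/σ)·√(45/2). Setting power to 80% gives σ of about 10.05 points, a standardised difference of about 0.60.
3. Stoppers measured: 50 per arm. If a share s stops and keeps a fraction f of the effect, the difference is 6·[1 − s(1 − f)] and the noncentrality is that difference divided by 10.05, times √(50/2). The SD is held constant.

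| Share stopping | Lost | Measured, full effect kept | Measured, half kept | Measured, none kept |
|---|---|---|---|---|
| 10% | 80.0% (45 per arm) | 84.0% (difference 6.0) | 80.2% (5.7) | 75.8% (5.4) |
| 20% | 75.1% (40 per arm) | 84.0% (6.0) | 75.8% (5.4) | 65.7% (4.8) |

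At the planned 10%, power changes by about 4 points in either direction. The figures for lost patients assume that they resemble those who remain, which is the assumption in doubt.

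**The case against.** The strongest reply is that the text does not make stopping stimulation the same as leaving the trial. A reader might infer that it does, and that patients who stop for side effects or by choice therefore yield no 6-month outcome. The documents do not support this. Withdrawal follows from stopping only where the patient also has an ablation. The patch is scheduled unconditionally. The retention section includes everyone who does not withdraw consent, and its closing phrase may simply mean the 6-month period, which *Follow-up schedule* calls the treatment duration. Participant request is listed as a ground for changing the intervention, not as withdrawal of consent. All of this stands.

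A reader might also try to put a size on the bias. Suppose 7 of 50 active patients stop and return to 15%, the other 43 are at 9%, and sham is at 15%. Dropping the stoppers gives 15 − 9 = 6.00 points. The assigned-arm mean is (43 × 9 + 7 × 15)/50 = 9.84%, a difference of 5.16, and 6.00/5.16 = 1.16, an apparent 16% overstatement. But the plan states LOCF. If those 7 stop before month 3 and give no later recording, baseline is carried, the mean is again 9.84% and there is no overstatement. It returns if they are excluded, or if an improved month-3 value of 9% is carried forward. The result depends on timing and on assumptions the documents do not supply, so no such figure can be attached.

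Finally, the article condenses a full protocol (version 6.0) that is not shown, and silence about follow-up after stopping would not be a finding by itself. That is right. What remains is that rules stated in the article point in different directions.

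**Conclusion.** The point holds as an inconsistency between stated rules that should be corrected. Consent withdrawals are left out in one section, while withdrawals are carried forward in another. Patients who stop and have an ablation are made study withdrawals. Foreseen loss of the primary outcome after complications is met only with documentation and LOCF. The phrase limiting the analysis to the course of treatment admits two readings. Applied as written, these rules can drop or replace 6-month values for reasons linked to tolerability or lack of benefit.

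The loss is avoidable, because the patch is already scheduled for every patient. Whether it would differ by arm is plausible but not shown, and neither the size nor the direction of bias can be calculated. The power range of 75.8% to 84.0% against 80.0% rests on the implied SD, a 6-point between-arm difference and 10% stopping in each arm. It shows only that sample size is not the main issue.

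**What to change.** - Reconcile the sections on discontinuing the intervention, retention, the *Statistical plan* and missing data, so that stopping or modifying stimulation and withdrawing consent to data collection are defined as separate events. This leaves the grounds for stopping untouched.
- In the retention section, delete the phrase limiting the analysis to the course of treatment. State that patients who stop or modify stimulation without withdrawing consent to follow-up keep the scheduled 3- and 6-month patch, SF-36 and adverse-event recording. Record the date of and reason for stopping, and analyse these patients in their assigned arm.
- For patients who do withdraw consent, keep the data collected up to that date where consent and local rules allow.
- State separately how values after ablation enter the primary analysis. This is a choice about which effect is estimated and does not follow from the changes above.

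**Cost.** Wording changes to the protocol and consent form; the visits and patches are already planned. The estimate may be less favourable because off-stimulation values are included, and power may fall as in the table above. Continued measurement helps only patients still in follow-up. *Trial status* gives recruitment from June 2021 with enrolment expected to finish on October 1, 2022, so on that timetable 6-month follow-up would end around April 2023. For patients already finished, only the analysis and data-retention parts of the change can apply.

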#### Data management

Each trial participant is assigned a unique eight-digit identification number that cannot be traced back to their proprietary information. Participant data, coded using these identification numbers, are stored in a central database which is a secure web-based platform designed for clinical trials. Clinical data are collected and input by trial staff. The principal investigator is responsible for ensuring the accuracy and completeness. During the study period, the principal investigator and a trained sub-investigator will have full access to the trial data. In addition, the monitor including the steering committee and data safety monitoring board will have access to the full dataset.

#### Confidentiality

All the participant data will be regarded as confidential. The investigator and members of research team must not disclose any information without prior written permission from the sponsor.

### Sample size calculation

Based on the 11 patients who underwent 1 month of stimulation, the average burden at baseline was 21.7% and the relative reduction after stimulation was 16.4%. We assume a baseline burden of 15% and expect a reduction of 40% at the end of 6 months. A sample size of 90 patients would provide at least 80% power to detect the specified effect sizes at a two-sided significance alpha level of 0.05. The sample size was calculated by using online statistic system (STATBOX, http://www.cnstat.org/statbox/; last access 9/19/2023). The exact formula used for sample size was as follows.$$1-{\varvec{\beta}}={\varvec{P}}{\varvec{\upgamma}}[{\varvec{F}}(1,{\varvec{N}}-2,{\varvec{N}}\{\left({{\varvec{\upomega}}}_{1}{{\varvec{\upomega}}}_{2}\right)[\frac{{{\varvec{\mu}}}_{1}-{{\varvec{\mu}}}_{2}}{{\varvec{\sigma}}}{]}^{2}\})\ge {{\varvec{F}}}_{\boldsymbol{\alpha }}]$$$${{\varvec{n}}}_{1}={{\varvec{N}}}^{\boldsymbol{*}}{{\varvec{\omega}}}_{1},\boldsymbol{ }{{\varvec{n}}}_{2}=\boldsymbol{ }{{\varvec{N}}}^{\boldsymbol{*}}{{\varvec{\omega}}}_{2}$$

To account for a potential drop-out rate of 10%, 50 patients in each group and 100 patients in total are planned to be recruited.

### Statistical plan

Descriptive statistics will be presented for baseline characteristics. Continuous variables are presented as mean ± SD or median (interquartile range), as appropriate. Categorical variables will be presented as proportions. Baseline variables will be compared between groups using Student’s *t*-test or Mann–Whitney *U* test for continuous variables and chi-square test for categorical variables. We will use a generalized estimating equation modelling approach to compare the outcome measure at the 3- and 6-month visits between the two groups after adjusting for the baseline measure [18]. Estimates reflect the exponentiated regression model terms and are interpreted as the ratio of the median responses in the active arm relative to the median response in the sham arm. Patients who discontinue the stimulation protocol and receive PVC ablation during the study period will be censored. These patients will be regarded as withdrawals from the study and the data from the last clinical follow-up will be included into final analysis.

Linear regression will be used to compare the association between the change in PVC burden at follow-up and measures of HRV and SKNA. Statistical significance will be set at *P* < 0.05 (two-sided). All statistical analyses will be performed using SAS software version 9.3 (SAS Institute, Cary, North Carolina).

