**Methods and design:**

The present study will be a prospective multicenter, double-blind, randomized, controlled trial to assess the antiarrhythmic effects of LLTS on frequent PVCs in patients without structured heart disease (SHD). A total of 100 patients with PVC burden > 10% will be randomly assigned to the active or sham LLTS in 1:1 fashion and receive the proposed intervention for 6 months. The primary outcome is PVC burden at 6 months as assessed by 10 days of continuous ambulatory electrocardiographic monitoring. Secondary outcomes include heart rate variability (HRV), quality of life, skin sympathetic nerve activity, and inflammatory markers. Adverse events will also be recorded.

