#### Relevant concomitant care and interventions permitted or prohibited during the trial

During the trial period, existing drug therapy will be continued with minimal changes possible. A change of medication during the treatment is not prohibited, but will be recorded as an event that requires additional modification.

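### Ablated patients are censored in a model where censoring is undefined, and the natural reading freezes a pre-ablation PVC burden as the month-6 outcome

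*Protocol article*

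**What the plan says.** The rule is two sentences in the Statistical plan: "Patients who discontinue the stimulation protocol and receive PVC ablation during the study period will be censored" and "These patients will be regarded as withdrawals from the study and the data from the last clinical follow-up will be included into final analysis".

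The outcome and model they apply to are:
- Abstract: "The primary outcome is PVC burden at 6 months as assessed by 10 days of continuous ambulatory electrocardiographic monitoring".
- Statistical plan: "We will use a generalized estimating equation modelling approach to compare the outcome measure at the 3- and 6-month visits between the two groups", adjusted for baseline. Exponentiated coefficients are read as a ratio of medians, active to sham.
- Follow-up schedule: outcome visits at 3 and 6 months only.

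Two other sections bear on the same patients:
- Methods in analysis to handle protocol non-adherence: "In case of withdrawals and missing data, the last observation carried forward procedure will be applied where appropriate", and "The analyses will be done in intention-to-treat population including all patients who received intervention or sham intervention without major protocol deviations".
- Plans to promote participant retention: "All study patients, except those who withdraw consent, will be included in the analysis during the course of treatment".

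The section on limitations of the design acknowledges that guidelines treat catheter ablation as first-line therapy for frequent, symptomatic PVCs in an otherwise normal heart. The article gives no expected ablation rate and no post-ablation burden.

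**The concern.** Censoring belongs to time-to-event data. A GEE for burden at months 3 and 6 has no censoring mechanism: a value is either used or missing. The next sentence then puts data from these patients back in, without saying whether the last follow-up must precede the ablation or which visit the value represents.

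The trigger is also a conjunction. A patient must both stop stimulation and be ablated. A patient ablated while still using the device is not covered, so the post-ablation burden would enter as an ordinary observation.

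Ablation acts directly on the primary outcome, and enrolled patients have symptomatic PVCs refractory to at least one drug. It is therefore a foreseeable event that plausibly follows failure of the assigned treatment and may differ in frequency between arms. The estimated ratio and its error rate then depend on how these patients are entered.

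**Working it through.** **1. What the wording allows.** The article has no figure of its own on this point, so the sections are set side by side.
- Statistical plan with the missing-data section: ablated patients are withdrawals, and withdrawals get the last observation carried forward. With visits only at months 3 and 6, the value standing in for month 6 is baseline (ablation before month 3) or month 3 (ablation later). This is the most natural reading.
- Statistical plan alone: the last clinical follow-up has no pre-ablation limit, so a post-ablation recording is not excluded.
- Missing-data section alone: the analysis set leaves out major protocol deviations. Whether ablation is one is not said, so such a patient might be dropped.
- Retention section: everyone except those who withdraw consent is analysed.

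**2. Inputs.** From the Sample size calculation: baseline burden 15% and a 40% reduction, so 15 × (1 − 0.40) = 9% and a ratio of 9/15 = 0.60 if sham does not change (assumption); 90 evaluable patients, so 45 per arm; and 90/(1 − 0.10) = 100 recruited, or 50 per arm.

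**3. Simulation of the readings.** All of the following are assumptions:
- Log-scale SDs are 0.6 at baseline and 0.4 within patient, with half the effect present at month 3.
- The ablated patients are those with the worst month-3 value relative to baseline.
- Post-ablation burden is about 1.5%.
- There are 50 patients per arm and 1,500 runs.
- The model is baseline-adjusted on log month-6 burden, which simplifies the GEE.

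Entries are the estimated ratio, with the two-sided 5% rejection rate in brackets where there is no true effect.

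| Ablated, sham / active | True ratio | Month 3 frozen | Baseline frozen | Post-ablation value entered |
|---|---|---|---|---|
| 10% / 10% | 1.00 | 0.999 (3.4%) | 1.001 (4.9%) | 1.003 (0.1%) |
| 10% / 2% | 1.00 | 0.950 (6.5%) | 0.998 (5.7%) | 1.185 (14.5%) |
| 20% / 4% | 1.00 | 0.926 (11.5%) | 1.000 (5.6%) | 1.403 (57.9%) |
| 4% / 20% | 1.00 | 1.080 (12.1%) | 0.997 (4.9%) | 0.711 (58.0%) |
| 10% / 2% | 0.60 | 0.574 | 0.604 | 0.719 |
| 20% / 4% | 0.60 | 0.561 | 0.614 | 0.859 |
| 4% / 20% | 0.60 | 0.685 | 0.663 | 0.474 |

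The Monte Carlo standard error of a 5% rate is √(0.05 × 0.95/1500) = 0.6 percentage points. Month-3 and month-6 deviations were independent given baseline, so month-3 freezing carries forward pure noise in patients picked for a bad reading. If bad readings persist, that bias would be smaller. Baseline freezing looks clean under no effect partly because no time trend was simulated.

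**4. Why near-zero values matter on a log scale.** If k of 45 sham patients enter at burden v, the sham geometric mean is multiplied by exp(k × ln(v/15)/45). Take k = 3 on sham and none on active (assumption):
- v = 0.5% (assumption): factor exp(3 × ln(0.5/15)/45) = 0.797, and 0.60/0.797 = 0.75.
- v = 0.05% (assumption): factor exp(3 × ln(0.05/15)/45) = 0.684, and 0.60/0.684 = 0.88.

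Under a log link on the mean, three patients at 0.5% give (42 × 15 + 3 × 0.5)/45 = 14.03, and 9/14.03 = 0.64. The distortion is large only if the outcome itself is logged.

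**The case against.** The strongest reply is that the two sections can be read as one rule: follow-up for the analysis ends at ablation and the last study value is carried forward. A reader might infer instead that ablated sham patients will be scored as the best responders. The documents do not support that as the plan's intention. It needs a follow-up after ablation to be counted as the last one, or a patient ablated while still stimulating. The text leaves both open but prescribes neither. The 0.75 to 0.88 figures belong to that less natural branch and also rest on an assumed post-ablation burden, an assumed three-to-none split and an assumed log-transformed outcome. A term pooled over months 3 and 6 would dilute them.

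On the natural reading the bias is modest, and with equal ablation rates the null estimate stays near 1. This stands, and it limits the size of the point.

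Three further inferences should not be drawn:
- That the choice will be made after the data are seen. A statistical analysis plan not shown here may fix it.
- That recordings stop after ablation. The article does not say so.
- That the exclusion of patients unwilling to stay on current drugs conflicts with "A change of medication during the treatment is not prohibited, but will be recorded as an event that requires additional modification". Willingness at entry and a recorded later change can coexist, and an analysis rule for drug changes may sit in the analysis plan.

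The reply does not remove the core. The article states a rule for ablated patients, and that rule uses an undefined term, leaves the timing of the included value open and omits one class of patients.

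**Conclusion.** The point holds. On the natural reading, a baseline or month-3 value is treated as the month-6 outcome in patients selected by treatment failure. At assumed ablation rates of 20% against 4%, month-3 freezing shifts a true 0.60 to 0.56 and takes the null rejection rate to 11.5%; with the rates reversed it gives 0.69 and 12.1%. It is therefore not reliably conservative. Baseline freezing does little under no effect, but dilutes 0.60 to 0.66 when ablation is commoner on active.

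The post-ablation branch could do much more damage, in either direction, but is a gap in the wording rather than what the plan says will happen. Every magnitude is illustrative, since the documents give neither an ablation rate nor a post-ablation burden. The plan should be changed because the rule governs the primary comparison and the correction is cheap.

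**What to change.** Replace the two sentences in the Statistical plan with one analysis rule for any ablation during the study period, whether or not stimulation stopped:
- All recordings before ablation enter the primary model; recordings after it do not.
- The last value is not carried forward. Later visits are set to missing and multiply imputed from baseline and pre-ablation burden.
- Ablation counts are reported by arm.
- One sensitivity analysis ranks ablation as the worst outcome. Imputation from sham-arm data may be added as a further one; it answers a different question and should not be the primary choice by default.

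Remove the word censored. Align the retention section and the section on non-adherence and missing data with this rule, including whether an ablated patient counts as a major protocol deviation. Fix the wording before arm-level outcomes are examined, particularly as the article lists the study statistician as unblinded.

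The cost is an imputation step, a little more analysis work and a slightly wider confidence interval. The imputation assumes that, given baseline and pre-ablation burden, ablated patients would otherwise have followed a course like that of comparable patients not ablated. The worst-rank analysis tests that assumption. No additional recordings are needed and clinical care is unchanged.
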